## 2. Background

Excessive salt intake is a primary cause of hypertension, yet individuals exhibit different degrees of salt sensitivity, i.e., the blood pressure response to salt intake. Salt sensitivity is known to be influenced by certain genetic variants. Therefore, identifying individuals with high salt sensitivity genotypes and providing them with personalized, gene-informed guidance may yield substantial health benefits. However, the evidence on the effectiveness of such interventions remains inconclusive.

Nielsen & El-Sohemy (2014) reported that a group receiving personalized advice including genetic information via monthly emails had reduced salt intake after 12 months compared to those receiving generic advice. Celis-Morales et al. (2017) found that personalized online advice delivered every three months led to reduced salt intake after 6 months, but incorporating genetic information did not significantly increase the effect. These interventions were not tailored to salt reduction and were conducted among general adults with relatively infrequent contact.

## 3. Objective and Significance

### 1) Objective

The objective of this study is to determine the effect of notifying individuals with salt sensitivity genotypes and delivering personalized dietary advice through the AI-based health app "*CALOmama PLUS*" on salt intake in individuals with elevated blood pressure.

### 2) Social Significance

The social significance of the study lies in the feasibility of identifying salt-sensitive genotypes through blood tests and the low-cost, high-frequency nature of app-based interventions. If the combination of genetic testing and app-based personalized dietary guidance effectively reduces salt intake, it may provide an efficient strategy to prevent hypertension.

## 4. Participant Selection

### 1) Setting: Employees of Toshiba Corporation

### 2) Inclusion Criteria

- Age 20–65
- Participants in Toshiba's genome and health data integration project, specifically those with AGT M235T genotype
- Systolic blood pressure  $\geq 120$  mmHg or diastolic blood pressure  $\geq 80$  mmHg in 2022 or 2023 health checkups
- No prior use of *CALOmama PLUS*
- Submitted spot urine sample and completed the pre-intervention survey

### 3) Exclusion Criteria

- Pregnant or lactating
- No smartphone (iPhone or Android)
- Cannot understand written Japanese

- Deemed ineligible by study investigators

#### 4) Sample Size and Rationale

A total of 451 participants are planned, with 208 allocated to the intervention group, 208 to the control group, and 35 to the app-only group. Celis-Morales et al. (2017) reported a 0.74g reduction in salt intake after 3 months in the intervention group compared to the control group. In addition, a systematic review by Huang et al. (2016) found that the standard deviation (SD) of estimated salt intake using the INTERSALT method from spot urine samples ranged from approximately 2.0 to 2.2g. Assuming an effect size of 0.74g and an SD of 2.2g, with a significance level of 5% and power of 90%, the required sample size for the primary comparison between the intervention group and the control group is 187 participants per group, totaling 374 participants. For the supplementary analysis comparing the intervention group and the app-only group, a sample size of 31 is required to obtain a 95% confidence interval of  $\pm 0.74$ g, assuming the same SD and significance level. Adding these together results in 405 participants, and allowing for a maximum dropout rate of 10%, the final sample size is set at 451 participants.

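### The app-only sample size of 31 does not give the stated ±0.74 g confidence interval against the intervention group; at SD 2.2 g the half-width is about ±0.84 g

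*Protocol*

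**What the plan says.** The Protocol, section 4, Sample Size and Rationale, first sizes the primary comparison of intervention with control. The inputs are "Assuming an effect size of 0.74g and an SD of 2.2g", "with a significance level of 5% and power of 90"%, and the result is "187 participants per group, totaling 374 participants". The SD comes from a cited systematic review in which it "ranged from approximately 2.0 to 2.2g".

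The same paragraph then sizes the third arm by precision. "For the supplementary analysis comparing the intervention group and the app-only group", it says that "a sample size of 31 is required to obtain a 95% confidence interval of" ±0.74 g, "assuming the same SD and significance level". The 31 is added to 374 to give 405, and the total is raised to 451 "allowing for a maximum dropout rate of 10"%. The allocation is 208, 208 and 35. No formula is given for the 31.

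**The concern.** The sentence describes a comparison of two groups, so its confidence interval must carry the sampling variance of both. At SD 2.2 g, 31 is too few even for a confidence interval of ±0.74 g around the app-only mean alone. It is further short once the variance of the intervention arm is added.

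This precision statement is the only basis given for the size of the app-only arm. By the table under Study Design (section 5), intervention against app-only is also the contrast that separates app use from genotype notification and salt-reduction content. A reader who relies on the stated ±0.74 g will credit that contrast with more precision than it has, and could read too much into a difference close to zero.

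**Working it through.** **Inputs, all from Sample Size and Rationale:** SD 2.2 g; 95% confidence; target half-width 0.74 g; completers 187 (intervention) and 31 (app-only); allocated 208 and 35.

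**1. The other figures in the paragraph reproduce.**
- Primary comparison: n per group = 2 × (1.96 + 1.2816)² × 2.2² / 0.74² = 185.7, so 186. The usual small-sample correction adds 1.96²/4 = 0.96, which gives 186.7, so 187 as stated. This uses the unadjusted SD of 2.2 g.
- Dropout: 187/0.9 = 207.8, so 208. 31/0.9 = 34.4, so 35. 208 + 208 + 35 = 451.

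The 31 is therefore the one figure that does not follow.

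**2. The stated comparison.** Half-width = 1.96 × SD × √(1/n₁ + 1/n₂).
- 187 against 31: 1.96 × 2.2 × √(0.005348 + 0.032258) = 1.96 × 0.4266 = **0.836 g** (0.841 g with the t quantile). 0.836/0.74 = 1.13, so 13% wider than stated.
- 208 against 35, nobody lost: 1.96 × 2.2 × √(1/208 + 1/35) = 0.788 g (t: 0.792 g).

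**3. App-only completers needed for ±0.74 g.** n₂ = 1 / [(0.74/(1.96 × 2.2))² − 1/187] = 1 / (0.029452 − 0.005348) = 41.5, so **42** (43 with t). After 10% dropout, 42/0.9 = 46.7, so 47 allocated, against the planned 35.

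**4. Other readings of the sentence.**

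| Reading | n needed for ±0.74 g | Half-width with 31 |
|---|---|---|
| Two groups, 187 in the other arm, SD 2.2 g | 42 (t: 43) | 0.836 g |
| Two groups, 187 in the other arm, SD 2.1 g | 38 | 0.798 g |
| Two groups, 187 in the other arm, SD 2.0 g | 34 | 0.760 g |
| Two groups of equal size, SD 2.2 g | 68 per arm | 1.095 g |
| 90% interval, 187 in the other arm, SD 2.2 g | 28 | 0.702 g |
| Single mean, SD 2.2 g | 34 (t: 37) | 0.774 g |
| Single mean, SD 2.1 g, z | 31 (30.9) | 0.739 g |
| Single mean, SD 2.0 g, t | 31 | 0.734 g |

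Among these unadjusted readings, 31 appears only for the mean of one group with an SD below 2.2 g. That may be its origin, but this is inference.

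**5. Power.** With 187 and 31 completers the standard error is 0.4266 g. Power for a true difference of 0.74 g is Φ(0.74/0.4266 − 1.96) = Φ(−0.225) = 0.41. The stated half-width, equal to the effect, would imply Φ(1.96 − 1.96) = 0.50.

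**6. Credit for analysis of covariance.** Baseline adjustment multiplies the SD by √(1 − ρ²), where ρ is the pre-post correlation. Reaching 0.74 g at 187 against 31 needs ρ = √(1 − (0.74/0.836)²) = 0.47, a residual SD of about 1.95 g.

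**The case against.** The arithmetic is hard to contest, but several points limit its weight.

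- **The comparison is supplementary.** The Protocol calls it so in both Sample Size and Rationale and Analysis Overview. The primary 187 per group and the 208/208 allocation do not depend on the 31. This stands.
- **Low power was largely accepted already.** A half-width equal to the design effect means about 50% power. The error takes this to about 41%, a loss of some 9 percentage points. This stands, and the 41% should not be read as wholly the result of the mistake.
- **Analysis of covariance is the planned method and will narrow the interval.** This is true in direction. But the paragraph states no correlation and says that the SD is unchanged, and the 187 was obtained without any such credit. The gain may be realised in the data; it does not support the figure as written.
- **The SD of 2.2 g is the top of the cited range.** At SD 2.0 g the half-width for 187 against 31 is 0.760 g, close to the target, and with full retention (208 against 35) it is 0.716 g, which meets it. That needs both a smaller SD than the one stated and no dropout.
- **No test or decision rule hangs on this comparison.** This is correct for the Protocol, so the risk of over-reading a null result concerns interpretation and not a planned decision.

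**Conclusion.** The concern holds. On the Protocol's own inputs (SD 2.2 g, 95% confidence, 187 and 31 completers) the half-width is about ±0.84 g, not ±0.74 g, and 42 to 43 app-only completers would be needed for the stated precision. If the difference observed were exactly 0.74 g, the interval would run from about −0.10 to 1.58 g and so include zero, whereas the stated precision would put its limit just at zero.

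The result assumes equal SDs in the two arms and no baseline adjustment, as in the primary calculation. With adjustment, the target is met only if the pre-post correlation reaches about 0.47. The error is confined to the supplementary comparison. It still needs correction, because it is the sole justification for the size of the app-only arm.

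**What to change.** Keep the 35 allocated to the app-only group and correct the precision statement in Sample Size and Rationale. Suggested text:

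> With 187 intervention and 31 app-only completers and an SD of 2.2 g, the 95% confidence interval for the difference between these groups has a half-width of about 0.84 g (power about 41% for a true difference of 0.74 g). This comparison is descriptive.

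If the sponsor wants to credit the gain from analysis of covariance, state the assumed pre-post correlation and the half-width that follows from it.

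This costs wording only. The stated precision becomes less favourable, but enrolment, allocation and the primary analysis stay as they are. Holding to ±0.74 g without adjustment would instead take about 42 app-only completers, or 47 allocated: 12 more than planned.

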### 5. Methods and Scientific Validity

#### 1) Study Design

This study is a three-arm parallel-group randomized controlled trial. Participants in the intervention group will be informed at the beginning of the trial that they carry a salt sensitivity genotype and will be asked to record their dietary intake using the *CALOmama PLUS* app. They will also receive weekly columns and quizzes related to salt reduction via the app. The control group will receive no intervention. The app-only group will be asked to record their dietary intake using the *CALOmama PLUS* app, but they will not be informed of their genetic information, nor will they receive any salt reduction content. Of the 451 study participants, 208 will be randomly allocated to the intervention group, 208 to the control group, and 35 to the app-only group. Over 600 individuals have already applied, ensuring the target sample size is attainable. Participants will not be informed of their group allocation (participant blinding). Evaluators at Kyoto University will also be blinded to group assignments (evaluator blinding).

|                                 | Control group
(n = 208) | App-only group
(n = 35) | Intervention group
(n = 208) |
|---------------------------------|----------------------------|----------------------------|---------------------------------|
| Genetic profile                 | ×                          | ×                          | ✓                               |
| CALOmama PLUS app use    | ×                          | ✓                          | ✓                               |
| Information on sodium reduction | ×                          | ×                          | ✓                               |

#### 2) Methods

Toshiba Corporation will recruit volunteers from among its employees and obtain informed consent via electronic signature through a dedicated website. Each consenting participant will be automatically assigned a study ID. Toshiba will verify that the consenting individuals are valid employees with internal email addresses, confirm their genotype and blood pressure, and notify eligible individuals of their study ID and the URL for the urine test.

Spot urine analysis will be conducted by Healthcare Systems Co., Ltd. (HS), commissioned by Wellmira Inc. Participants will input their ID, name, address, email address, healthcare utilization status, and health awareness responses into a form accessed via the URL provided by Toshiba. HS will mail test kits for both pre- and post-intervention collection and conduct the initial urine analysis. HS will report the ID, email address, health awareness and medical visit survey responses, and test results to Wellmira. Wellmira will then report the ID, health awareness and medical visit responses, and urine submission status to Toshiba.

Toshiba will finalize participants based on urine submission and survey completion, and randomly assign them into the three groups. Toshiba will generate a participant list with IDs, allocation groups, and health check data from 2023 (sex, age, height, weight, systolic and diastolic blood pressure) and provide this to Wellmira.

Wellmira will inform participants in the intervention group that they carry a salt sensitivity genotype and request that they log every meal in the *CALOmama PLUS* app. Weekly columns and quizzes on salt sensitivity and salt reduction will be delivered via the app. Participants in control group 2 will be asked to record their meals using the app but will not receive genetic information or salt reduction content. The intervention period using *CALOmama PLUS* will last for 3 months.

At the end of the trial, Toshiba and Wellmira will instruct participants to submit post-intervention urine samples using the pre-mailed kits and complete a follow-up survey via a URL. Information collected will include ID, health awareness, age, weight, systolic and diastolic blood pressure (if measurable), and medical visit status. HS will report post-intervention urine test results to Wellmira and notify participants of their own pre- and post-test results.

Wellmira will provide Kyoto University with anonymized data including participant ID, allocation group, sex, pre- and post-intervention urine test results, health awareness, age, height, weight, blood pressure, and medical visit status. Group labels will be coded as Group A, B, or C to maintain evaluator blinding. Once the analysis is complete and results are confirmed, evaluator blinding will be lifted—no later than two months after data delivery. Toshiba recruits participants and obtains e-consent. Participants are screened for eligibility and randomized into three groups. Spot urine samples are analyzed by Healthcare Systems Co., Ltd. under contract from Wellmira Inc. Health behavior and awareness surveys are conducted online. Wellmira manages intervention content and data anonymization. Kyoto University conducts analysis in a blinded manner.

### 3) Measures and Schedule

#### i. Measurement items, methods, and agencies

- a. Salt intake before and after the intervention will be measured by HS, commissioned by Wellmira Inc., using spot urine tests. Sodium, creatinine, and potassium excretion will be analyzed. Kyoto University will estimate daily salt intake using the INTERSALT formula adjusted for BMI and age. If samples are not submitted by the deadline, Wellmira will follow up with participants.
- b. Behavior change intentions and healthcare utilization before and after the intervention will be assessed via online surveys based on the transtheoretical model. The question will be “What do you think about improving eating habits?” with options: 1 = “Not interested”, 2 = “Need to improve but cannot do it”, 3 = “Want to do it now”, 4 = “Have been implementing improvements for less than 6 months”, or 5 = “Have been implementing improvements for more than 6 months”. Medical visit status will be surveyed similarly. If responses are not submitted on time, Wellmira will follow up. Pre-intervention surveys will be administered by HS, post-intervention by Wellmira.
- c. Post-intervention age, weight, and systolic/diastolic BP will be collected via online survey by Wellmira. If values differ greatly from baseline health check data, Wellmira will contact participants for confirmation. Reminders will be sent for unsubmitted surveys.
- d. Pre-intervention age, sex, height, weight, and blood pressure will be provided by Toshiba

based on 2023 health check data.

ii. Measurement Schedule

| Date                                   | Events                                                                                                                                                                                                                     |
|----------------------------------------|----------------------------------------------------------------------------------------------------------------------------------------------------------------------------------------------------------------------------|
| March 29, 2024-July 3, 2024            | Obtain consent for participation                                                                                                                                                                                           |
| July 30, 2024                          | Submit spot urine and complete survey (approx. 1 minute)                                                                                                                                                                   |
| September 10, 2024
(start of trial) | Intervention group: Notified of salt-sensitive genotype and asked to log meals in CALOmama PLUS for 3 months
Control group: No action
App-only group: Asked to log meals in CALOmama PLUS for 3 months |
| December 9, 2024
(end of trial)     | All participants: Submit spot urine and complete survey (approx. 1 minute)
Control and app-only groups: Notified of salt-sensitive genotype
Control group: May begin using CALOmama PLUS if desired           |

4) Analysis Overview

The primary analysis will compare the intervention group to the control group. A supplementary analysis will compare the intervention group to the app-only group to assess the effect of *CALOmama PLUS* use alone.

- i. Primary Outcome: Sodium intake
- ii. Secondary Outcomes: Behavior change intentions, systolic and diastolic blood pressure, BMI
- iii. Main Analytical Method: Analysis of covariance

6. Study Duration

1) Recruitment Period

From the date of institutional approval to July 3, 2024

2) Intervention Period

Three months from the date of recruitment

3) Study Period

From the date of institutional approval to March 31, 2026

7. Informed Consent

Toshiba Corporation will set up a dedicated website accessible only to its employees, through which it will provide explanations about the study and obtain electronic signatures on the informed consent form from interested participants. The company will offer opportunities for participants to ask questions about the study content and will provide adequate answers. After obtaining informed consent, participants will have continued access to the consent materials. Printed documents will be provided upon request.

8. Handling of Personal Information

1) Types of Personal Information Collected

Personal information

2) Creation Period and Method

In July 2024, when participants are finalized, Toshiba will generate an ID list electronically. This list will be managed and stored by individuals within Toshiba who are not involved in this study, and study personnel will not have access to it.

3) Types of Personal Information Retained and Security Measures

Each institution will manage personal data as follows. Data will be encrypted with passwords and either transported on secure hard drives or transferred via encrypted file transmission systems. All data will be analyzed on computers equipped with security software, stored in physically locked rooms.

|                | Toshiba | Wellmira | HS | Kyoto Univ. |
|----------------|---------|----------|----|-------------|
| Name/Address   | ×       | ×        | ✓  | ×           |
| Age/Sex        | ✓       | ✓        | ✓  | ✓           |
| Study ID       | ✓       | ✓        | ✓  | ✓           |
| Email          | ×       | ✓        | ✓  | ×           |
| Health Checkup | ✓       | ✓        | ×  | ✓           |
| Urine Results  | ×       | ✓        | ✓  | ✓           |
| Survey Results | ×       | ✓        | ✓  | ✓           |

4) Data Management Responsibility

Department of Social Epidemiology, Graduate School of Medicine and School of Public Health, Kyoto University  
[name] (part-time researcher)

5) Handling of Data Upon Withdrawal of Consent

If a participant withdraws consent before data analysis begins, Wellmira will delete the relevant data and not provide it to Kyoto University. If data has already been transferred, Kyoto University will delete it. Once data analysis is complete and blinding is lifted, consent cannot be withdrawn. This is clearly stated in the consent form.

9. Risks, Burdens, and Benefits

1) Burdens and Risks

Participants will submit spot urine samples and complete surveys before and after the intervention. Those in the intervention and app-only groups will be asked to log meals using the *CALOmama PLUS*. Additionally, being informed of one's salt-sensitive genotype may cause anxiety.

2) Benefits

Participants will receive notifications of their estimated salt intake after the study. Those in the intervention group will learn their genotype at the start, while participants in the control and app-only groups will be informed after the trial. All participants will eventually have access to the *CALOmama PLUS* app and AI-based dietary advice.

3) Overall Risk-Benefit Assessment

This non-invasive study is considered low burden, especially in comparison to prior similar studies.

4) Risk Minimization Measures

Questions about genetic results will be answered based on physician-supervised guidance. Participants needing further support will be referred to the Department of Genetic Medicine at Kyoto University Hospital.

221 10. Sample and Data Storage and Disposal

222 1) Storage Duration

223 Samples and data will be stored for 10 years after the study concludes, in accordance with  
224 institutional policies.

226 2) Storage Method

227 i. Toshiba

228 Data will be stored on electronic media, in a locked safe installed in a security-enhanced  
229 area of the company equipped with surveillance cameras. Entry to this area is restricted  
230 by biometric authentication and electronic locks to prevent access by unauthorized  
231 individuals. For analysis purposes, a dedicated analysis computer located within this  
232 secure area will be used in a completely offline (disconnected) state. The analysis  
233 computer will be periodically connected to internal servers protected by the company's  
234 firewall to update antivirus software and operating system patches, managed by the  
235 administrator.

237 ii. Wellmira

238 Personal data will be stored on Wellmira's dedicated internal server for personal  
239 information. Access to this server is strictly limited to the designated personal  
240 information manager and a small number of authorized personnel within the company.  
241 The server is located in a security room equipped with surveillance cameras and  
242 electronic locks to control entry and exit, managed under the supervision of the personal  
243 information manager. The server is also regularly connected to internal management  
244 servers within the firewall for antivirus and OS updates. To respond to inquiries, the  
245 research-specific email addresses, group allocation information (intervention, control  
246 group, app-only group), and participant IDs are temporarily stored. Additionally, the  
247 post-trial survey data, which is collected via Google Forms, will be temporarily stored  
248 on Google Workspace cloud storage. After the response deadline, the survey form will  
249 be immediately transferred to Wellmira's secure internal server, and all data will be  
250 permanently deleted from the cloud. Any information received from Toshiba or  
251 Healthcare Systems Co., Ltd. that is encrypted with passwords—whether transported via  
252 hard drive or file transmission systems—will also be transferred to the secure server.  
253 Urine samples collected by HS on behalf of Wellmira will not be stored after  
254 measurement and will be immediately discarded.

256 iii. Kyoto University

257 Data will be stored on a computer installed with security software. This computer will be  
258 located in a physically locked room to prevent unauthorized access.

260 3) Post-Retention Disposal

261 Data will be permanently destroyed using irreversible methods at separate locations.

263 4) Data Transfer and Logging

264 When data is shared between institutions, detailed records of the transaction, including dates,  
265 recipient institutions, responsible persons, and data types, will be maintained and stored  
266 securely.

268 11. Secondary Use and Data Sharing

269 Study data may be shared with researchers, public health authorities, and other non-profit entities for  
270 medical or scientific advancement, subject to agreement among Kyoto University, Toshiba, and Wellmira.

Ethics review will be required prior to any secondary use. Participants will be notified by email and may opt out.

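### Follow-up of missing post-intervention urine samples is assigned to the party that knows the allocation, and nothing requires it to be blind to arm

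*Protocol*

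**What the plan says.** **Follow-up of samples.** Section 5. 3) i. a covers the urine samples before and after the intervention and gives one rule for late ones: "If samples are not submitted by the deadline, Wellmira will follow up with participants". It sets no number, timing, wording or channel of reminders, and it does not say that the sender must be unaware of the arm.

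**Who knows the arm.** Under section 5. 2), Toshiba randomises and gives Wellmira a list of IDs with allocation groups. Section 10. 2) ii adds that Wellmira temporarily keeps allocation together with email addresses and IDs to answer inquiries. Wellmira also runs the app content (section 5. 2)), is a co-investigator (section 13. 2)) and shares ownership of the results (section 21). Section 5. 1) describes blinding of participants and of the Kyoto University evaluators only.

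**Who handles the samples.** On the urine kits, section 5. 2) says: "HS will mail test kits for both pre- and post-intervention collection and conduct the initial urine analysis". HS also reports the post-intervention results. The table in section 8. 3) shows HS holding names, addresses, emails, study IDs and urine results. HS is not listed in section 5. 2) as a recipient of allocation.

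**Contact during the trial.** From 10 September to 9 December 2024 the intervention arm logs meals and gets weekly columns and quizzes, and the app-only arm is asked to log meals. The schedule's entry for controls at the start is "Control group: No action". At the end, section 5. 2) has Toshiba and Wellmira jointly instruct participants to submit the second sample, and the schedule lists this for all participants.

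**Allowance for loss.** Section 4. 4) uses one figure for all arms: "allowing for a maximum dropout rate of 10" per cent.

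**The concern.** The primary comparison, intervention against control, rests on a single follow-up urine sample per person. Anyone who does not return it contributes no observed outcome. If the effort to recover late samples varies with the arm, even unintentionally, those with an outcome are no longer the groups that were randomised. Blinding the evaluators at Kyoto University does not help, because the selection happens before the data reach them.

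The protocol places this step with the party that has both the allocation and an interest in the result. Wellmira has an established channel to the two app arms and none of that kind to controls. With no fixed reminder rule, equal handling depends on goodwill, and it could not be shown afterwards that it took place.

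**Working it through.** **1. The plan's own figures.** Inputs from section 4. 4): "Assuming an effect size of 0.74g and an SD of 2.2g", and "with a significance level of 5% and power of 90" per cent. A two-sided test is assumed, since sidedness is not stated.

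- Normal approximation: n = 2 × [2.2 × (1.960 + 1.282) / 0.74]² = 185.7, so 186 per group. The t-test version gives 186.7, so 187. This matches the stated result: "is 187 participants per group, totaling 374 participants".
- Inflation for 10% loss: 187 / 0.9 = 207.8, so 208; 31 / 0.9 = 34.4, so 35; 208 + 208 + 35 = 451. This matches section 5. 1): "208 will be randomly allocated to the intervention group, 208 to the control group, and 35 to the app-only group".

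The sample size is not at fault here.

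**2. Time over which samples can be lost.** From 10 September to 9 December 2024 is 20 + 31 + 30 + 9 = 90 days. From the 30 July baseline date to 9 December is 1 + 31 + 30 + 31 + 30 + 9 = 132 days.

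**3. Power.** With 10% lost in each arm, 187 and 187 remain and power is 90.2%. With 5% and 15% lost (assumed), about 198 and 177 remain and power is again 90.2%. Unequal loss at this level costs essentially no power, and it still averages to the planned 10%, so the overall dropout figure would not reveal it. The issue is bias.

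**4. Bias in a comparison of completers.** Let m be the proportion missing in an arm and g the mean salt intake of non-submitters minus that of submitters, taken as equal in both arms. The completers' mean is then the full arm's mean minus m × g. With no true effect, the difference between arms is off by

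bias = (difference in m between arms) × g.

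Assumptions, none of them from the protocol: a difference in loss of 0.10 (5% against 15%) and g of 0.25, 0.5 or 1 SD. The SD is the protocol's 2.2 g. Numbers remaining are 208 × 0.95 = 197.6 and 208 × 0.85 = 176.8, so SE = 2.2 × √(1/197.6 + 1/176.8) = 0.228 g.

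| g | Bias | Share of 0.74 g | True error of a two-sided 5% test |
|---|---|---|---|
| 0.25 SD (0.55 g) | 0.055 g | 7% | 5.7% |
| 0.5 SD (1.1 g) | 0.11 g | 15% | 7.7% |
| 1 SD (2.2 g) | 0.22 g | 30% | 16.2% |

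With equal loss and equal g, the bias is zero. All these figures are before baseline adjustment. Section 5. 4) names analysis of covariance, and adjusting for baseline salt intake would remove the part of g that baseline explains.

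**5. Direction.** It turns on two unknowns, which arm loses more and the sign of g. If non-submitters eat more salt and controls are lost more often, control completers look too good and the benefit is understated. If the app arm is lost more often, the benefit is overstated.

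**The case against.** A reader might infer more than this: that controls are left without contact until the final sample while both app arms are kept engaged, so that retention effort is unequal by design and control loss will be higher. The documents do not support that reading.

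- Columns, quizzes and meal logging are the treatment, and no action is the comparator. They are not retention steps, and unequal contact comes with any no-intervention control.
- The retention steps that are described are common to all arms. The end-of-trial instruction goes to everyone, with the employer as joint sender, and the late-sample rule makes no distinction by arm. The protocol nowhere says that reminders go through the app.
- Pushed weekly content is stated for the intervention arm only. Continuing contact in the app-only arm is an inference from the request to log meals.
- Higher control loss is not implied. Controls are due their genotype result and optional app access at the end, while the app arms carry three months of logging. Everyone had already returned a urine sample and a survey before randomisation, which removes some of the least engaged.
- The late-sample sentence also covers the baseline sample, which precedes randomisation and cannot cause differential loss.
- The loss rates and gaps in the calculation are assumptions. The upper end needs a threefold difference in loss and non-submitters a full SD away.

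All of this stands, and it limits the point to one of risk. It does not answer the remaining gap: a rule that reads the same for all arms is still carried out by a party that knows the arm, with no schedule to hold it to. Handling of missing data may be set out in an analysis plan not shown here, but analysis repairs such selection only in part. Who collects the outcome is fixed in this protocol.

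**Conclusion.** The point holds in a limited form. Follow-up of missing post-intervention samples, on which the primary outcome depends, is given to a party that holds the allocation, delivers the intervention and shares ownership of the results. Nothing makes that follow-up blind to arm.

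Differential loss is a possibility and not a planned feature. The documents give neither its direction nor its size. The 0.06 to 0.22 g range is an illustration that rests on an assumed 10-point difference in loss, an assumed gap of 0.25 to 1 SD common to both arms, and no credit for baseline adjustment. It shows that the matter is worth a cheap safeguard, not that the trial is biased. This is a low-cost improvement and not a correction of an error.

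**What to change.** In section 5. 3) i. a, leave the rule for the baseline sample as it is. For the post-intervention sample, replace follow-up by Wellmira with a rule of this kind:

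*HS sends reminders for the post-intervention urine sample by email, triggered only by non-receipt of the sample, on the same fixed dates and in the same wording for all three arms. HS has no access to allocation. The app is not used for these reminders.*

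The number and dates of reminders should be written in. The end-of-trial instruction from Toshiba and Wellmira can stay, since it already goes to all participants.

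HS is a practical choice because it already holds the addresses and IDs and receives the samples. Two cautions apply. HS is commissioned by Wellmira, so it is not organisationally independent. That it lacks the allocation is inferred from its absence among the listed recipients, so the protocol should state it outright.

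The cost is a small change to the HS contract and a few automated emails. The sample size, the outcome and the analysis do not change.
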